## Abstract

**Background:**

Subsyndromal generalized anxiety is highly prevalent and associated with impaired well-being, elevated stress, and functional limitations, yet affected individuals often do not meet criteria for guideline-based treatment. Scalable, low-threshold digital interventions that target psychophysiological regulation may help address this gap. Guided self-hypnosis and aromatherapy using essential oils have each demonstrated anxiolytic and relaxation-promoting effects. Combining these approaches may enhance efficacy and allow for conditioning of relaxation responses via olfactory cues.

**Methods:**

This study protocol describes a randomized controlled trial evaluating the efficacy and conditioning potential of a digital self-hypnosis intervention combined with essential oil inhalation in adults with subsyndromal generalized anxiety. A total of *N* = 630 participants will be randomized into six groups. Four groups enter the primary efficacy analysis: (1) self-hypnosis + bergamot essential oil, (2) self-hypnosis + lavender essential oil, (3) self-hypnosis without essential oil, and (4) a minimal-intervention control. The intervention is delivered online over six weeks (Phase 1), followed by a two-week conditioning phase without hypnosis (Phase 2), in which stimulus-specific effects of the essential oils are tested. The primary outcome is subjective relaxation, measured by the Multidimensional Mood Questionnaire (MDBF) at baseline, post-intervention (6 weeks), and post-conditioning (8 weeks). Secondary outcomes include anxiety symptoms, perceived stress, sleep quality, well-being, and worry. In a voluntary subsample, heart rate variability (HRV) and pulse wave variability (PWV) will be assessed as physiological correlates of relaxation. In addition, the questionnaires are expanded to include open-ended questions, enabling an exploratory assessment of participants’ experiences, attitudes, and reflections on the intervention and its potential for sustainability. This approach complements quantitative results with qualitative insights and may reveal new perspectives for future research.

**Discussion:**

This study is expected to provide evidence on the efficacy of essential oil-enhanced digital hypnosis for subsyndromal anxiety and will examine whether repeated pairing of hypnosis and olfactory stimulation induces conditioned relaxation responses. If effective, this multimodal, low-intensity intervention could represent a scalable preventive approach for individuals with increased anxiety who are not receiving formal treatment and have been medically diagnosed.

**Clinical Trial Registration:**
https://www.drks.de/search/de/trial/DRKS00039047/details, Identifier DRKS00039047.

## Introduction

1

Adults with subsyndromal generalized anxiety often experience significant distress and impairment comparable to those with clinical generalized anxiety disorder (GAD) (1). Despite this burden, these individuals may not qualify for standard treatments and thus benefit from accessible, preventive interventions. Self-help techniques like relaxation training, mindfulness, or hypnosis delivered digitally offer promising avenues for supporting this group. In particular, hypnosis and hypnotherapy have demonstrated effectiveness in reducing anxiety and stress. Reviews find that hypnotherapy can significantly lower anxiety levels and simultaneously modulate the autonomic nervous system by reducing sympathetic arousal and increasing parasympathetic tone (2). This physiological shift under hypnosis is associated with relaxation and could potentially be cardioprotective (2).

Aromatherapy with essential oils is another complementary strategy shown to alleviate anxiety. For example, inhalation of lavender (*Lavandula angustifolia Mill.*) essential oil has repeatedly been found to reduce stress and anxiety and improve mood in various populations (3–5). Likewise, bergamot (*Citrus bergamia*) essential oil-rich in limonene, linalool, and linalyl acetate-has demonstrated calming, anxiolytic effects. Clinical studies report that bergamot oil aromatherapy can lower heart rate and blood pressure and reduce stress and anxiety levels (6–8). These essential oils are generally safe and well-tolerated, making them suitable for a wide application in anxiety relief settings (9). Importantly, lavender and bergamot have distinct aromatic profiles and chemical compositions, allowing researchers to compare their effects on relaxation. Both oils' anxiolytic properties, documented in the literature, provide a strong rationale for their use in a stress-reduction intervention.

Combining guided self-hypnosis with essential oil inhalation may yield synergistic benefits for relaxation. Hypnosis can induce a deep relaxation response, and pairing this state with a specific olfactory stimulus (the essential oil's aroma) opens the door for classical conditioning of relaxation. Through repeated pairings, the neutral scent of an essential oil could become a conditioned stimulus (CS) that evokes calmness even in the absence of hypnosis. In fact, prior work has explored hypnotherapeutic olfactory conditioning, where patients undergoing hypnosis learn to associate a pleasant odor with feelings of safety and control (10). Preliminary results using this technique in cases of post-traumatic stress showed promise that the scent alone later helped induce relaxation and reduce anxiety (10). This concept aligns with fundamental Pavlovian conditioning principles and suggests that a well-timed combination of aromatherapy and hypnosis could train individuals to self-soothe by simply inhaling the scent after conditioning.

The present study builds upon a successful trial in healthy individuals (11) and aims to rigorously test a multimodal relaxation intervention in subsyndromal anxiety. The predecessor study was a four-arm randomized trial with over 500 participants, which found that combining web-based self-hypnosis with an essential oil significantly increased subjective relaxation compared to either technique alone. Participants who received the combined hypnosis plus essential oil reported notably greater improvements on relaxation scales with moderate effect sizes relative to controls. Encouraged by these findings, this study will extend this approach to individuals with mild generalized anxiety symptoms and examine not only the acute efficacy but also the conditioning effect of the essential oil over time. In summary, the study's primary goal is to evaluate whether digital self-hypnosis combined with inhalation of an essential oil, either lavender or bergamot, can produce greater relaxation and anxiety reduction than hypnosis alone or minimal intervention, and secondarily to determine if the essential oil's scent can become a stand-alone cue for relaxation after repeated pairing with hypnosis as well as whether objective physiological measures such as heart rate variability (HRV) can prove a relaxation effect on the autonomic nervous system.

## Methods and analysis

2

### Study design

2.1

This study is designed as a randomized, controlled trial with six parallel groups, conducted fully online, except for optional physiological measurements (Figure 1). The intervention spans 8 weeks in two phases. Phase 1 (weeks 1–6) involves guided self-hypnosis sessions delivered via an online platform (SoSci Survey, Version 3.5.02, SoSci Survey GmbH, Munich, Germany) with concurrent essential oil aromatherapy in certain groups. Phase 2 (weeks 7–8) involves exposure to the essential oil alone without hypnosis to test conditioned relaxation responses. The trial was registered in the German Clinical Trials Register (Deutsches Register Klinischer Studien, DRKS; ID: DRKS00039047) on January 20, 2026. All procedures were approved by the Institutional Review Board of Charité – Universitätsmedizin Berlin (Ethikkommission der Charité, Campus Charité Mitte, reference number EA2/244/25) and were conducted in accordance with the Declaration of Helsinki (1975, as revised in 2008) and relevant local data protection regulations.

**Figure 1 F1:**
[figure not shown]
Study overview and timeline. After online screening (GAD-7/PHQ-9), eligible participants are randomized (1:1:1:1:1:1) to six arms. Phase 1 (Acquisition; 6 weeks) involves self-hypnosis every ∼2 days, with or without essential oil exposure depending on group; pre/post-session relaxation is recorded via VAS. Phase 2 (Evocation; 2 weeks) tests conditioned responding: participants in aroma arms complete essential-oil exposure without hypnosis every ∼2 days (CS match = same oil as in Phase 1; CS mismatch = switched oil), with VAS recorded pre/post exposure. Assessments are conducted at baseline (T0), post-phase 1 (T1), and post-phase 2 (T2); follow-up surveys occur at 6 and 12 months without further application. An optional Berlin/Brandenburg subcohort undergoes exploratory physiological assessment (HRV, PWV) at the time points indicated. CS, conditioned stimulus; GAD-7, generalized anxiety disorder-7; PHQ-9, patient health questionnaire-9; HRV, heart rate variability; PWV, pulse wave variability; VAS, visual analogue scale.

### Participants

2.2

The target population is adults (18–65 years) in Germany with subsyndromal generalized anxiety. Key inclusion criteria are: (a) GAD-7 anxiety questionnaire score between 1 and 7, indicating minimal to mild anxiety, not meeting GAD diagnostic threshold, (b) no acute psychiatric condition requiring treatment, and (c) willingness and ability to follow the 8-week intervention schedule online. Participants must reside in Germany, have sufficient German language skills, since all materials are in German, and provide informed consent online. To ensure safety, individuals are excluded if they screen positive for any serious mental health issues, such as moderate-to-severe anxiety or depression [e.g., GAD-7 ≥15, Patient Health Questionnaire (PHQ)-9 ≥20, or PHQ-9 suicidal ideation item > 1, which suggest clinical severity] (12, 13), current psychotherapy or psychiatric treatment, or a history of conditions like psychosis, bipolar disorder, post-traumatic stress disorder, or severe personality disorder. Participants with known scent sensitivities or olfactory impairments are also excluded specifically for anyone with an intolerance or aversive reaction to lavender or bergamot essential oil, or diagnosed anosmia (loss of smell), cannot take part. This screening is implemented via an initial online questionnaire (including GAD-7 and PHQ-9) before randomization. Only those who pass the screening thresholds and report no disqualifying conditions are granted access to the study portal. This procedure ensures the sample truly comprises people with subclinical anxiety levels and avoids enrolling anyone in need of more intensive treatment. If a prospective participant's responses indicate high symptom severity or risk, the system automatically excludes them and provides standardized feedback recommending appropriate help such as contacting a physician or therapist, thereby prioritizing safety.

### Recruitment

2.3

Participants will be recruited from the general public in Germany, reflecting the subsyndromal nature of the target condition, which typically does not lead to routine clinical referral. Recruitment will be conducted via online channels (e.g., social media advertisements, study-participation platforms) and offline postings (e.g., flyers in primary care practices, dental practices, pharmacies, and community settings such as libraries, community centers, and health- and mindfulness-related venues). Interested individuals will access an online screening survey (GAD-7, PHQ-9 and eligibility items); only eligible participants will be enrolled and randomized. Participation is voluntary and not remunerated. As non-financial compensation, participants in aromatherapy arms will keep the essential oil stick and essential oil, and all participants will receive access to the self-hypnosis audio files after completing the final assessment, to support continued self-care if desired.

### Safety procedures and participant contact

2.4

The intervention is fully self-administered via the online platform; no therapeutic interaction is provided. Participants can contact the study team at any time for study-related questions. Eligibility is determined through a rule-based online screening (GAD-7, PHQ-9, treatment status, and safety-relevant history). Individuals exceeding predefined safety thresholds (e.g., GAD-7 outside the inclusion range; PHQ-9 ≥20; PHQ-9 item 9 > 1; or self-reported history of psychosis, bipolar disorder, post-traumatic stress disorder (PTSD), or severe personality disorder) are automatically excluded and receive standardized information recommending appropriate professional support and crisis resources. In rare borderline or ambiguous cases, a brief structured safety call (approx. 3–5 min) is conducted by psychology-trained study staff to confirm that participation in a low-intensity self-help intervention is appropriate. This safety call is not diagnostic or therapeutic. Enrollment proceeds only if no indications of treatment-requiring symptom severity are present.

### Interventions

2.5

#### Procedure

2.5.1

In Phase 1 (weeks 1–6), participants practice digital self-hypnosis every two days (approx. 3–4 sessions per week) using audio recordings delivered through the SoSci web interface. Each session involves listening to a guided hypnosis audio; the first session is ∼22 min long, and subsequent sessions last ∼11 min each. The hypnosis script focuses on inducing relaxation and calm, those used in the earlier study (11), and it is standardized across participants aside from the experimental manipulations of essential oil. Participants are instructed to find a quiet, comfortable place for each session and to listen to the audio using headphones or speakers without interruption.

Simultaneously, groups 1, 2, 5, and 6 combine these hypnosis sessions with aromatherapy using an essential oil. Those assigned to an aromatherapy condition receive a small aroma stick (inhaler) infused with either Lavender essential oil or Bergamot essential oil, depending on group, to use during the sessions. They are instructed to inhale from the aroma stick at the beginning of each hypnosis session and intermittently breathe in the fragrance as needed throughout the audio, allowing the olfactory stimulus to be present during the hypnotic relaxation. By pairing the specific essential oil with the hypnosis-induced relaxation repeatedly over 6 weeks, the intervention seeks to create a strong mental association between that smell and the relaxed state.

After six weeks of regular practice, Phase 1 concludes with the T1 assessment. Immediately thereafter, Phase 2 (weeks 7–8) begins, lasting two additional weeks. In Phase 2, participants no longer do the hypnosis sessions; instead, they engage in essential oil exposure alone every two days, continuing with the same schedule of thrice weekly exposure. During these sessions, they will inhale from the aroma stick, containing an essential oil, for a brief period (several minutes) but without any accompanying audio or hypnosis. The purpose is to test whether the essential oil itself can elicit a relaxation response after the conditioning in Phase 1. Some groups will receive the same oil in Phase 2 as they did during Phase 1 (matched condition), while others will receive a different oil (mismatched condition) to test the stimulus specificity of the conditioned response. No explicit relaxation exercise is given in this phase aside from the essential oil exposure. Participants still rate their mood before and after each essential oil exposure, as described below, to gauge any relaxation effect purely from the scent.

#### Essential oil dosing and essential oil stick standardization

2.5.2

To ensure consistent dosing across participants, aromasticks (PRIMAVERA LIFE GmbH, Germany; Article No. 60009) with standardized absorbent cotton wicks (100% cotton fleece) will be used. These aroma sticks are designed for self-filling and controlled inhalation and are supplied with identical wick material and housing components. Participants will be instructed to apply 3–5 drops of the assigned essential oil to a fresh cotton wick, in accordance with the manufacturer's standardized instructions. The impregnated wick will then be inserted into the aroma stick and sealed using the designated closure mechanism. This dose range corresponds to the manufacturer's recommended dosage for personal inhalation use. Participants will receive standardized instructions for aromastick handling and use illustrated as step-by-step guide included in the shipment.

Based on manufacturer guidance and prior experience, the essential oil intensity of a single application persists for approx. two days, after which participants will be instructed to re-apply the same standardized dose using a new wick. This dosing schedule corresponds directly to the intervention frequency (every two days), ensuring consistent exposure across participants and sessions.

All participants will receive identical aroma stick kits, essential oils, and illustrated step-by-step instructions based on the manufacturer's original usage protocol. Participants will confirm correct preparation and refill procedures via a checklist integrated into the online study platform. The selection of essential oils and dosing procedures was informed by expertise in pharmacognosy and aromatherapy within the research team and supported by the product-specific handling recommendations of the supplier. The supplier had no role in study design, data collection, analysis, interpretation, or publication decisions.

### Study groups

2.6

Participants are randomly assigned to one of six groups (arms) in a 1:1:1:1:1:1 ratio. Four groups are primary comparison arms for the main efficacy analysis at 6 weeks, and two additional groups are included for secondary analyses of conditioned stimulus specificity in Phase 2.

**Group 1: Hypnosis** + **Essential Oil (Bergamot).** Participants receive the self-hypnosis audio and inhale bergamot essential oil during each session in Phase 1. In Phase 2, they continue with bergamot oil only (no audio) on the same schedule. This is a conditioned stimulus (CS)-match condition where the same essential oil is used for conditioning and testing.

**Group 2: Hypnosis** + **Essential Oil (Lavender).** Participants receive the hypnosis audio plus lavender essential oil inhalation during Phase 1 sessions. In Phase 2, they use lavender oil only without hypnosis. This is the CS-match for lavender.

**Group 3: Hypnosis Only (No Oil).** Participants receive guided hypnosis sessions in Phase 1 with no aromatherapy. This controls for the effects of hypnosis alone. They do not use any aroma in Phase 2 either and effectively have no active intervention in weeks 7–8.

**Group 4: Minimal Intervention Control.** Participants do neither hypnosis nor essential oil in Phase 1. Instead, they may receive a minimal activity just to match time/expectation. This arm serves as a baseline and expectancy control. They also do not receive any aroma in Phase 2.

**Group 5: Hypnosis** + **Oil (Bergamot) → Switch to Lavender.** These participants start identical to Group 1 (hypnosis + bergamot oil in Phase 1). However, in Phase 2 they experience a CS-mismatch by switching to lavender without hypnosis. This group helps test if a different scent can trigger relaxation or if the effect is lost when the conditioned stimulus changes. It serves as a control for Group 1 in the conditioning analysis.

**Group 6: Hypnosis** + **Oil (Lavender) → Switch to Bergamot.** These participants mirror Group 2 initially (hypnosis + lavender in Phase 1), then switch to bergamot oil only in Phase 2, creating a CS-mismatch. This serves as a control for Group 2 to assess stimulus specificity.

All groups 1, 2, 5, and 6 receive the full combined intervention (hypnosis + essential oil) in Phase 1, ensuring that Groups 5 and 6 have the same conditioning opportunity as their counterparts before the switch. Groups 3 and 4 allow us to isolate the effects of hypnosis itself (Group 3) and to account for any changes over time not attributable to the interventions (Group 4). Randomization is implemented via the SoSci Survey platform's built-in algorithm once participants are deemed eligible, ensuring allocation concealment. Because of the nature of the interventions, participants will know if they are using an oil or not (blinding is not feasible on the user level), but they will not be informed of the study hypotheses regarding which combination is expected to be most effective. The trial is single blinded in that the data analysts/statisticians will remain blind to group labels until after the primary analyses are completed, to prevent bias in outcome analysis.

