### Data analysis

2.13

The primary outcome (MDBF calmness subscale change from T0 to T1) will be analyzed using an ANCOVA model. The model will include the study group (4 arms for primary analysis: Groups 1–4) as the independent variable and the baseline MDBF score as a covariate to control for any initial differences and improve statistical power. This aligns with the principle of analyzing covariance to account for baseline variance. The primary contrast of interest is whether either of the two combination groups (1: Hypnosis + Bergamot, 2: Hypnosis + Lavender) differ significantly from the control groups (3: Hypnosis-only, 4: Minimal intervention) in adjusted mean relaxation at T1. We anticipate a significant overall group effect; planned pairwise comparisons with appropriate correction for multiple comparisons, if needed, will examine specific differences, especially 1 vs. 3, 2 vs. 3, and combined 1&2 vs. combined 3&4. The primary hypothesis will be supported if Groups 1 and 2 show statistically greater increases in relaxation than Group 3 and Group 4 (*p* < .05, two-tailed).

For Phase 2 conditioning effects, a similar ANCOVA or mixed-model approach will be used at T2. The analysis will focus on the four groups that underwent Phase 2 aroma testing (Groups 1, 2 with match vs. Groups 5, 6 with mismatch). We will compare relaxation outcomes at T2 among these, using T1 values as covariates. A significant difference (e.g., match > mismatch) on the MDBF relaxation change from T1 to T2 or on the Phase 2 VAS responses would support H2.1. We may also use repeated measurements ANOVA or multilevel modeling incorporating all three time points (T0, T1, T2) to examine group × time interactions across the full study duration. The VAS data from each session will be analyzed using linear mixed-effects models, which can handle multiple observations per participant. These models will test differences in immediate relaxation gain per session by group and can also model time trends (session number as a predictor) to see if there is a significant upward trend in pre-session relaxation over the 6 weeks for each group (learning effect).

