## Discussion

3

This study is a comprehensive trial examining a novel multimodal intervention that integrates digital self-hypnosis with essential oil aromatherapy for individuals suffering from persistent worries and stress at a subclinical level. By leveraging the anxiolytic properties of lavender and bergamot essential oils in tandem with the deep relaxation of hypnosis, the study aims to enhance stress reduction outcomes and potentially condition a natural relaxation trigger, the essential oil, that participants can use beyond the intervention. The significance of this research lies in its preventive focus, because helping those with mild anxiety manage their symptoms effectively and possibly avert progression to a clinical disorder (1). If successful, the intervention could be a low-cost, easy to use tool, the essential oils are inexpensive, and the hypnosis can be delivered via an app or website, empowering individuals to self-regulate anxiety and stress in their daily lives.

Furthermore, the study will contribute to the scientific understanding of mind-body interactions, confirming whether the addition of a sensory cue can reinforce hypnotic relaxation and create lasting conditioned effects. Previous evidence shows that pleasant odors can directly influence mood and physiology (3–5, 32) and pairing them with therapy techniques may harness the brain's associative learning to prolong benefits. The outcome of this study will inform not only clinical practice in terms of combining aromatherapy with psychological interventions, but also theoretical models of how contextual cues such as essential oil can become safety signals or relaxation triggers through conditioning. A positive finding would open avenues for personalized aromatherapy in mental health, such as patients could choose an essential oil, they find comforting to integrate into their therapy, thus creating a portable cue for calm that they carry into real-world situations. The anticipated conditioning effects of lavender and bergamot essential oils are assumed to arise from their olfactory properties and the associated scent stimulus that elicit the conditioned response. Potential stress-reducing and anxiolytic pharmacological effects of the oils' bioactive constituents are not accounted for and may, however, have contributed to the observed effects that are attributed to conditioning.

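### The pairwise controls named for the conditioning test differ in Phase 2 oil, and the analysis section does not fix the pooled match-versus-mismatch contrast that would remove the oil effect

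*Protocol article*

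**What the plan says.** Section 2.6 (Study groups) sets the Phase 2 oil for the four aroma arms. For Group 1 (bergamot in Phase 1): "In Phase 2, they continue with bergamot oil only (no audio) on the same schedule". For Group 2 (lavender in Phase 1): "In Phase 2, they use lavender oil only without hypnosis". For Group 5 (bergamot in Phase 1): "However, in Phase 2 they experience a CS-mismatch by switching to lavender without hypnosis". Group 6 goes from lavender to bergamot.

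The same section assigns pairwise controls. Of Group 5 it says "It serves as a control for Group 1 in the conditioning analysis", and of Group 6 "This serves as a control for Group 2 to assess stimulus specificity". The stated reason is that the members of each pair have had the same conditioning before the switch.

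Sections 2.9 (Outcomes) and 2.10 (Hypotheses) describe the key Phase 2 comparison as the matched groups (1 and 2) against the mismatched groups (5 and 6). Section 2.13 (Data analysis) names the same two sets and then says: "We will compare relaxation outcomes at T2 among these, using T1 values as covariates". As support for H2.1 it accepts "A significant difference (e.g., match > mismatch) on the MDBF relaxation change from T1 to T2" or on the Phase 2 VAS responses. The Discussion adds that "Potential stress-reducing and anxiolytic pharmacological effects" of the oils are not accounted for and may contribute to what is attributed to conditioning.

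**The concern.** Within each named pair, being matched coincides completely with inhaling one particular oil in the test phase. Group 1 differs from Group 5 in match status and also in bergamot versus lavender; Group 2 differs from Group 6 in match status and also in lavender versus bergamot. The Introduction treats both oils as calming in their own right, with different compositions whose effects can be compared, so the protocol itself allows for a direct difference between them.

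Section 2.13 does not close this route. It compares outcomes among four groups and gives match over mismatch only as an example of a supportive difference. A four-group test, or one of the pairs named in 2.6, could meet that wording through an oil difference alone. The trial could then report conditioning for one oil where there is none, and miss it for the other. Groups 5 and 6, which are 2 × 105 = 210 of the 630 planned participants, were added for this question.

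**Working it through.** The protocol states no figure for this contrast, so there is none to reproduce. The check is on what each contrast estimates, followed by illustrative rejection rates.

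**Inputs from the protocol article.** Oil sequences are from 2.6 (B = bergamot, L = lavender): Group 1 = B→B, Group 2 = L→L, Group 5 = B→L, Group 6 = L→B. From 2.11: 105 per arm, two-sided alpha 0.05, dropout up to about 35% (105 × 0.65 ≈ 68), covariate explaining about 20% of variance. That last figure is stated for the baseline covariate in the primary analysis; using it for T1 in Phase 2 is an assumption.

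**Assumed.** The documents give no direct difference between the oils in Phase 2. The range shown is 0.2 to 0.4 SD.

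**Step 1: expected Phase 2 responses.** Let c be the match effect, d the direct bergamot-minus-lavender effect of the Phase 2 oil, and g the bergamot-minus-lavender effect carried over from Phase 1. Relative to lavender in both phases without a match effect:

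- Group 1 = c + d + g
- Group 2 = c
- Group 5 = g
- Group 6 = d

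**Step 2: contrasts.**

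| Contrast | Estimates | Oil that differs |
|---|---|---|
| 1 vs 5 (named in 2.6) | c + d | Phase 2 |
| 2 vs 6 (named in 2.6) | c − d | Phase 2 |
| 1 vs 6 | c + g | Phase 1 |
| 2 vs 5 | c − g | Phase 1 |
| (1 + 2)/2 − (5 + 6)/2 | c | neither |

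The last row is (2c + d + g)/2 − (g + d)/2 = c. It is the Phase 1 oil by Phase 2 oil interaction, and its value is the same however the arms are paired. If d = c and g = 0, the named pairs read 2c and 0: bergamot appears to condition and lavender does not, although the match effect is the same for both.

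**Step 3: rejection rates with c = 0 and g = 0, no covariate adjustment.** For a pair, the noncentral t parameter is d × √(n/2). At d = 0.3 and n = 105 it is 0.3 × √52.5 = 2.17. For the four-group F test with 3 numerator df, the means lie at ±d/2, so the noncentrality is 4n × (d/2)² = n × d². At d = 0.3 and n = 105 it is 105 × 0.09 = 9.45.

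| d (SD, assumed) | Named pair, n = 105 | Named pair, n = 68 | Four-group test, n = 105 | Four-group test, n = 68 |
|---|---|---|---|---|
| 0.2 | 30% | 21% | 37% | 25% |
| 0.3 | 58% | 41% | 73% | 52% |
| 0.4 | 82% | 64% | 94% | 79% |

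If the T1 covariate removes 20% of variance (residual SD √0.8), the pair figures at n = 105 rise to about 37%, 68% and 90%, so the table is on the low side. The two named pairs move in opposite directions: one imitates conditioning, the other hides it.

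**Step 4: the pooled contrast.** In 3,000 simulated ANCOVAs per setting, with Phase 2 oil effects of 0, 0.2 and 0.4 SD and equal arms of 105 or 68, the pooled contrast was significant in 4.6% to 5.1%, the nominal level.

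**Step 5: unequal dropout.** A pooled mean weighted by participants is not exactly free of d. With assumed completers of 75 and 65 in Groups 1 and 2, and 70 and 70 in Groups 5 and 6, d = 0.3 leaves a bias of 0.3 × (75/140 − 70/140) ≈ 0.011 SD. This is small, and equal arm weights remove it.

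**The case against.** The strongest reply is that the protocol's main conditioning comparison is already sound. Sections 2.9, 2.10 and 2.13 all set Groups 1 and 2 against Groups 5 and 6, each side has one arm of each oil in each phase, and Step 2 shows the oil effect cancelling. This stands. A reader might infer that the conditioning analysis as a whole takes an oil difference for conditioning; the documents do not support that, because no passage makes a single pair or a four-group test decisive. H2.1 is also directional and covers both oils, so a pure oil effect would contradict it in one of the two pairs.

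A reader might also infer that 2.6 names the wrong controls and that the pairs should be 1 with 6 and 2 with 5. That does not hold either. The named pairs hold the Phase 1 oil constant, for a stated reason, and ask a legitimate question: whether the response is lost when the scent changes. The other pairs hold the Phase 2 oil constant but differ in the Phase 1 oil. The two risks are not quite equal, since a Phase 1 oil effect present at T1 can be adjusted for, at least in part, by the T1 covariate, whereas a Phase 2 oil effect arises later. Still, neither pairing alone isolates the match effect.

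The Discussion's caveat is not simply mistaken. H2.1 also predicts a pre-to-post VAS rise within the matched groups, and there a direct oil effect cannot be separated from conditioning.

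An exact contrast formula is often left to an analysis plan that is not shown. The point here is narrower: the published text labels confounded pairs as controls for the conditioning analysis and words its criterion for support openly enough to admit them.

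**Conclusion.** The concern holds as a problem of labelling and of an unfixed test. The pairs named in 2.6 are each confounded with Phase 2 oil (c + d and c − d). The pooled comparison that the protocol points to is not confounded, given additive oil effects and equal arm weights, but 2.13 leaves room for other differences among the four groups to count as support for H2.1.

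The size depends on an oil difference that the documents do not give. At an assumed 0.3 SD with no conditioning and 105 per arm, the rates are about 58% for a named pair and 73% for a four-group test, against about 5% for the pooled contrast. If the oils do not differ directly, nothing is lost. If conditioning strength differs by oil, the pooled contrast estimates the average. Novelty of the scent in the switched arms is a separate matter that no pairing removes.

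H2.1 is secondary, and the primary comparison of Groups 1 to 4 at T1 is unaffected. This should be fixed before analysis, but it is not a must-fix.

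**What to change.** - **Section 2.13:** analyse Groups 1, 2, 5 and 6 as a 2×2 of Phase 1 oil by Phase 2 oil, with both oil main effects in the model. Make the equal-weight match-versus-mismatch contrast (the interaction) the only between-group test of H2.1, on the MDBF and on the Phase 2 VAS. State that an oil main effect, a four-group omnibus difference or a single pair does not support H2.1.
- **Section 2.6:** describe Groups 5 and 6 jointly as the mismatch controls for Groups 1 and 2. Report any pairwise contrast (1 vs 5, 2 vs 6, 1 vs 6, 2 vs 5) as descriptive, noting which phase's oil differs.
- **Discussion:** say that direct (additive) oil effects are separated from conditioning in the between-group match-mismatch contrast, but not in the within-group pre-to-post change.

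The cost is wording in three places and two model terms. No arm, participant or measurement changes.
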